### Evaluation of the implementation approach

The four core components of the intervention are defined as the essential functions that are hypothesized as necessary to produce outcomes in a typical service setting [37]. If the core components are not upheld, then the intervention will not function optimally.

Building on a large body of practice-change evidence in support of active rather than passive implementation efforts,^34,58^ we will guide each program site through a facilitated, staged, change process informed by implementation science. We expect that sites will vary somewhat in the timing of implementation activities. Sites will proceed through four stages of implementation based on the QIF/Meyers^59^ and described in detail below. Sites will create operational implementation teams that will execute implementation activities and report on implementation progress during monthly check-in-calls with the research team. Achievement of key implementation process milestones will be recorded, and monthly discussion calls will flag where more implementation support may be needed. The phases of our implementation process (Table 4) include:

**Table 4 Tab4:** Summary of implementation process

Stage 1	Stage 2	Stage 3	Stage 4
0–3 months	0–3 months	4–24 months	24–36 months
Meet with leads at each site and navigators Review transition program practice profile	Create site implementation teams and meet monthly for coaching calls Identify and secure any necessary organizational supports/resources	Meet monthly with site implementation teams Gather process feedback, document implementation progress (strategies, challenges)	Meet with study sponsor to discuss scale up/national implementation Meet with site implementation teams to discuss full implementation at sites

Stage 3. *Initial implementation and Evaluation of Implementation Quality*: Each site will begin delivery of the intervention. Process feedback and progress notes, and staff meetings will inform any refinements to the implementation and service delivery processes and address any staff support/skill building needs. To increase the fidelity of the implementation process across sites, we will use a checklist derived from the Quality Implementation Framework to track adherence to implementation stages and activities that have been tailored to our program and context. Each site will document progress, strategies, and challenges in relation to these tasks. Here, we will be mindful of site-specific factors and population-specific factors (e.g., sex, gender, ethnicity, rural vs. urban, LGBTQ status) that may influence implementation. In addition to implementation process tracking data, staff feedback will be used to refine the implementation process in an ongoing fashion.

Stage 4. *Full Implementation and Sustainability***:** At this stage, the transition intervention should be partially embedded at the participating centers and managed with existing resources. Once effectiveness of the intervention has been demonstrated, sites will assess the feasibility of full implementation (with their IBD clinicians) and sustainment using internal or external resources. Planning for sustainability will be embedded throughout all stages to build capacity ongoingly and ensure the intervention can be fully implemented and scaled up in their site and in other sites.

### Outcome measures

See Table 5 for summary of primary and secondary outcome measures.

**Table 5 Tab5:** Primary and Secondary Outcome Measures. Note: Primary and secondary outcomes will be measured at enrollment (T1), at the time of transfer to adult care (T2), and at the end of the study period (1–2 years after transfer) (T3), unless otherwise specified

Domain	Measure	Timing of administration
*Primary outcome*		
Disability and function	IBD-DI [26, 27]	T1, T2, T3
*Secondary outcomes*		
Transition readiness	Transition Readiness Assessment Questionnaire (TRAQ) [28] Transition Success Scores (TSS)	T1, T2, T3
Bio-psychosocial risk	Pediatric IBD INTERMED [24]	T1, T2, T3
Disease-related knowledge	IBD-KID2[29]	T1, T2, T3
Quality of life	IBDQ-32[57]	T1, T2, T3
Self-efficacy	IBD Self-Efficacy Scale—Adolescent (IBD-SES-A) [58]	T1, T2, T3
Mental Health	Patient Health Questionnaire-9 (PHQ-9) Generalized Anxiety Disorder-7 (GAD-7)	T1, T2, T3
Disease activity	Physician global assessment (PGA) of disease activity Modified Harvey Bradshaw Index (HBI) Assessment for CD Activity [44] Pediatric Ulcerative Colitis Activity Index (PUCAI) for UC Activity [45] Fecal calprotectin *(at enrollment and study termination only)*	T1, T2, T3 T1, T3
Health services utilization	Emergency department visit after 18th birthday (yes/no) Number of emergency department visits after 18th birthday Hospitalization after 18th birthday (yes/no) Number of outpatient visits to GI after 18th birthday	T3

#### Aim 1 (effectiveness of the intervention)

Primary Clinical Outcome: Functioning: We will use the IBD Disability Index (IBD-DI) summary score [42, 43], an ordinal variable that measures participant functioning as the primary outcome. IBD-DI was selected as a validated measure of overall disability, functioning, and health. The primary outcome will be measured 3 years after enrollment.

Secondary Clinical Outcomes: The secondary outcomes measure transition readiness and program success, assessment of the five domains of health with emphasis on biopsychosocial risk, mental health, quality of life, and self-efficacy. In addition, by determining a marker of inflammation (i.e. fecal calprotectin) and disease activity (i.e. Harvey-Bradshaw Index [44] or Pediatric Ulcerative Colitis Activity Index [45]), we will assess whether the intervention improves overall remission rates. See Table 1 for a list of secondary outcomes.

Health Services Utilization and Cost: Study data will be deterministically linked to provincial health administrative data health at ICES (Toronto, Canada) and PopDataBC (Vancouver, Canada) using provincial health card numbers. Health service utilization will be tracked through the transfer of care by linking to physician billing, hospitalization and emergency department databases. To assess the effect of a transition intervention program on health services utilization after transfer to adult care with the potential that the intervention provides health system cost effectiveness while maintaining good health will be an important determination.

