**Fig. 1 Fig1:**
[figure not shown]
Patient flow

Inclusion criteria: We will enroll adolescents aged 16–17.5 years with IBD diagnosed > 6 months before recruitment using standard criteria [20]. Since most adolescents are transferred to adult care around 18 years of age, this would allow for at least one year of post-transfer follow-up due to the 3-year length of the grant funding. Study participants must have the ability to speak/read English at a functional (Grade 8) level, intention to reside in Canada after transfer to adult care, and ability to use a smartphone or personal computer for the virtual intervention components. In Canada, > 95% of adolescent IBD patients in Canada have access to technology to complete study requirements [21, 22].

Exclusion criteria: Adolescents who do not fluently speak English, those intending to leave Canada after graduation from high school, and those unwilling to be involved will be excluded. We will maintain a record of ineligible patients, and those who declined enrollment and the reasons for doing so, to inform the feasibility of post-RCT implementation in clinical practice.

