#### Core component 1: individualized assessment

Each enrolled patient will undergo an individualized assessment of their biopsychosocial risk profile (Pediatric IBD INTERMED [24]), self-efficacy (IBD-SES-A) [25], functioning (IBD-DI) [26, 27], transition readiness (TRAQ) [28] and IBD knowledge (IBD-KID2) [29], administered by the transition navigator (see below) or research staff. In addition, supplemental questionnaires will be administered to assess depression, anxiety, and activation (i.e., a participant’s level of engagement in their own care); these will be self-administered by the participant with subsequent review by the transition navigator (Table 1).

**Table 1 Tab1:** Tools used for individualized assessment and corresponding domains

Core skills	Questionnaire	Domains
*Main questionnaires*		
Coping/self-regulation*	IBD Disability Index (IBD-DI)	Functions, Activity participation, Structures, Environmental factors
Comprehensive	Pediatric IBD INTERMED	Biological, Psychological, Social, family/caregiver, Health systems
Assertiveness/self-efficacy	IBD Self-efficacy Scale for Adolescent (IBD-SES-A)	Self-confidence, Health-related quality of life
Tasks/knowledge	Transition Readiness Assessment Questionnaire (TRAQ)	Self-management, Self-advocacy
	Inflammatory Bowel Disease Knowledge Inventory Device Version 2 (IBD KID2)	Knowledge
*Supplementary questionnaires*		
Depression	Patient Health Questionnaire-9 (PHQ9)	
Anxiety	Generalized Anxiety Disorder-7 (GAD7)	

The INTERMED, PHQ9, and GAD 7 may be repeated as needed by the navigator to establish progress and update participants’ risk profile

The Pediatric IBD INTERMED is a validated instrument that assesses five domains of health (biological, psychological, social, family/caregiver and health system) reflecting historical/developmental, current state and future prognosis/vulnerability [24]. The instrument is is designed to facilitate inter-professional clinical communication and should identify issues related to the different domains of health. Identified psychosocial needs will be addressed by the care team, and/or in the skill-building component. The Pediatric IBD INTERMED and supplemental questionnaires may be repeated as determined by the navigator to establish progress and update the patient’s psycho-social risk profile.

All questionnaires will be administered at study enrollment, the time of transfer to adult care, and intervention completion.

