Maintenance phase: 2 months after randomization→ 1–2 years after transfer	The frequency of the virtual meetings during the maintenance phase will be flexible, with a minimum of 2 visits per year, depending on the needs and willingness of the AYA In the year around transfer (from 6 months prior to transfer, to 6 months after transfer), a minimum of 3–4 meetings will be planned A detailed script will be provided to the navigators to ensure a standardized list of topics are covered. The navigator will also work with the AYA and healthcare team to address deficits based on the AYA’s answers. Example questions to be asked by the navigator include: How are you finding the quality of your health care? How are things going with the biologic infusion clinics and the Patients Services Program (if applicable) How are you filling your prescriptions? How are the cost of your prescriptions covered? Do you know how to work with your insurance company to ensure your medications are covered? How did your visit with the doctor go? Did you parents go with you? How was your visit with the adult doctor? Did you find her/him approachable and knowledgeable? Did you feel you had enough time with the doctor? Did the adult doctor talk to you about colonoscopy, and how that might differ from colonoscopy in a pediatric hospital? What are you plans for post-secondary school work/university/college? Have you investigated your university’s disability program, and any accommodations to which you might be entitled because of your IBD?
Conclusion phase: end of study	Ongoing feedback of clinical and psychosocial concerns with adult GI Intervention completion will depend on patient readiness and the success of the skill-building exercises (*Core Component 3*), typically 1–2 years after transfer depending on age at enrollment Final assessments will be administered by the navigator at the final visit (*Core Component 2*), and the AYA will be instructed on how to complete the outcome measures

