### Statistical analysis

The primary outcome is the IBD-DI ordinal measure at the end of the treatment period (1–2 years after transfer). We will compare groups using the Wilcoxon-Mann–Whitney test, and statistical significance set at P < 0.05.

Secondary outcome measures will be analyzed at study completion and interim time points by comparing participants in the intervention and control arms using Wilcoxon-Mann–Whitney test. In addition, repeated measures analysis will determine changes over time for the primary and secondary outcome measures at three timepoints (baseline, time of transfer, end of study).

Assessment of health services outcomes will be conducted by linking clinical to health administrative data. Likelihood of emergency department use and hospitalization after transfer will be compared using multivariable logistic regression analysis. Number of ED and outpatient visits will be determined using either Poisson regression or negative binomial regression. All models will include confounders reported in Canadian health services studies of IBD patients: age at diagnosis, age at transfer, sex, rural/urban household, and socioeconomic status.

Assessment of implementation outcomes will be determined using mixed methods (quantitative and qualitative) assessment, as described above.

Sample size calculation: The IBD-DI ranges in score from 0–100. The categories of disability are 0–20 (no disability), 20–35 (mild disability), 35–50 (moderate disability), and 50–100 (severe disability). In the original validation study of the IBD-DI, the mean score of patients was 35.3 ± 20.5. We would consider the goal of this transition program to allow AYAs to achieve a mean level of < 20 (no disability), presenting a 16-point decrease from the mean baseline, or a Cohen effect size (*d*) of 0.78.

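### The time of the primary outcome is stated in ways that cannot all hold, and one of them could tie the intervention arm's final IBD-DI to success of the intervention

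*Protocol article*

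**What the plan says.** The protocol article gives several times for the final IBD-DI:

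- **Aim 1, Primary Clinical Outcome:** "The primary outcome will be measured 3 years after enrollment".
- **Outcome measures, note to Table 5:** T3 is "at the end of the study period (1–2 years after transfer) (T3), unless otherwise specified".
- **Statistical analysis:** "The primary outcome is the IBD-DI ordinal measure at the end of the treatment period (1–2 years after transfer"). The window is that of Table 5, but it is attached to the end of treatment rather than the end of the study.
- **Core component 1**, whose instruments include the IBD-DI: "All questionnaires will be administered at study enrollment, the time of transfer to adult care, and intervention completion".
- **Table 2, Conclusion phase** (intervention arm): "Intervention completion will depend on patient readiness and the success of the skill-building exercises", "typically 1–2 years after transfer depending on age at enrollment", and "Final assessments will be administered by the navigator at the final visit".
- **Control Group**, under core component 4: the same assessment is given for the last time at termination of the study, with no readiness or success condition.

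The inclusion criteria set enrollment at 16 to 17.5 years, put transfer at around 18, and say of this age range that "this would allow for at least one year of post-transfer follow-up due to the 3-year length of the grant funding". The primary test is a Wilcoxon-Mann–Whitney comparison of the two arms, with no adjustment described for when the assessment took place.

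**The concern.** The time of measurement is part of the definition of a primary outcome. Two things are at stake.

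First, with competing definitions, two sites could measure the same participant at different times, and which measurement counts as primary could be settled after data are seen.

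Second, the wording about completion exists for one arm only. If it decides when the last IBD-DI is taken, an intervention participant may be measured once judged ready, while a control is measured by a different clock. The trial is unblinded, and nothing stated for the primary analysis would correct for that.

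This is not detail left to an analysis plan. The article states the time more than once, and the statements disagree.

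**Working it through.** **Inputs.** Enrollment age *a* = 16.0 to 17.5 and transfer age *A* of about 18 (inclusion criteria); final assessment 3 years after enrollment (Aim 1) or 1–2 years after transfer (Table 5, Statistical analysis).

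**The plan's own figure.** The inclusion criteria promise at least one year after transfer. The youngest enrollee followed for three years reaches 16.0 + 3 = 19.0, which is 19.0 − 18.0 = 1.0 year after transfer. The figure reproduces, provided each participant has the full three years.

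**Aim 1 against Table 5.** Years after transfer at 3 years from enrollment = 3 − (*A* − *a*). With *A* = 18.0:

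| Enrollment age | Enrollment to transfer (y) | 3 y from enrollment, in y after transfer | Inside 1–2 y? |
|---|---|---|---|
| 16.0 | 2.0 | 1.0 | yes |
| 16.5 | 1.5 | 1.5 | yes |
| 17.0 | 1.0 | 2.0 | yes |
| 17.25 | 0.75 | 2.25 | no |
| 17.5 | 0.5 | 2.5 | no |

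The definitions agree from 16.0 to 17.0 and conflict above 17.0. The share in conflict is (17.5 − 17.0)/(17.5 − 16.0) = 1/3 if enrollment ages are uniform (an assumption).

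**Sensitivity to transfer age** (uniform enrollment ages):

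| Transfer age | 3 y from enrollment, in y after transfer | Share outside 1–2 y |
|---|---|---|
| 17.75 | 1.25–2.75 | 50% |
| 18.0 | 1.0–2.5 | 33% |
| 18.25 | 0.75–2.25 | 33% |
| 18.5 | 0.5–2.0 | 33% |

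No single transfer age reconciles the two. The enrollment range spans 17.5 − 16.0 = 1.5 years, so times after transfer also span 1.5 years, and the window is only 2 − 1 = 1 year wide.

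**The completion wording.** No arithmetic applies here. Core component 1 ties the last questionnaires to intervention completion. Table 2 ties completion to readiness and skills success, and has the navigator give final assessments at the final visit. The Statistical analysis section calls the primary time the end of treatment. Read together, these let success influence when the intervention arm is measured. The control-group text has no counterpart.

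**Reachability.** A participant enrolled at grant month *m* reaches 3 years at month *m* + 36. If data collection stops at month 36 (an assumption; the article does not say so), only *m* = 0 fits.

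**The case against.** The strongest reply is that Aim 1, Table 5 and the Statistical analysis section are the places that define the primary outcome, and each gives one nominal time for both arms. The Table 2 sentence on completion goes on to say "typically 1–2 years after transfer depending on age at enrollment", which names a baseline variable as setting the usual time, and its row is labelled as the end of the study. Table 2 also mentions outcome measures that the participant completes, apart from the navigator's final assessments.

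Much of this stands, and it limits what can be claimed. A reader might infer that the arms are in fact measured at different times and that the comparison favors the intervention. The documents do not show that: it follows only if the completion wording governs. Early completers might be measured sooner and slow ones later, and no course of the IBD-DI over time is given, so even the direction is unknown.

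Three other inferences also go too far:

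- The 1–2 year window could put T3 anywhere from 1.5 years after enrollment (age 17.5: 0.5 + 1) to 4.0 years (age 16.0: 2.0 + 2). That spread comes largely from age, affects both arms, and should balance by randomization.
- Nothing in the text says that the intervention moves the transfer date; transfer is described as driven by age.
- Late enrollees cannot be said to become missing outcomes, because no accrual schedule or end of data collection is given.

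The reply does not remove the conflict above age 17.0. Nor does separating outcome measures from navigator assessments settle the matter, because the IBD-DI is listed both as a core component 1 instrument and as the primary outcome.

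**Conclusion.** The concern holds as an inconsistency in the primary time point, with a possible arm-specific trigger. Aim 1 conflicts with Table 5 and the Statistical analysis section for enrollment above 17.0, by up to 2.5 − 2.0 = 0.5 year beyond the window, assuming transfer at 18.0. Under each of the four transfer ages tried, at least one third of a uniform enrollment range falls outside the window.

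Comparability of T3 between arms is not assured, and the primary comparison could be biased if measurement follows completion; the documents do not establish that it is. The conflict in wording is certain. Its effect on the result cannot be quantified from the article. It should be settled before enrollment, and the Data Availability statement says recruitment had not begun at submission.

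**What to change.** State one primary T3 for both arms, fixed in advance from a date that allocation cannot move, with a stated window, and independent of readiness or intervention completion. Two anchors already in the article would serve:

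- **Three years after enrollment**, as in Aim 1. Time since randomization is then equal for all; time after transfer runs from 1.0 to 2.5 years (transfer at 18.0).
- **A set time after the 18th birthday**, the date from which Table 5 counts service use. Age is then equal for all; time since enrollment varies. At 12 months after the birthday, for example, it is 19.0 − *a*, or 3.0 years at age 16.0 and 1.5 years at 17.5.

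Align Core component 1, the Conclusion phase of Table 2, the control-group text, Table 5, Aim 1 and Statistical analysis to the choice. Keep any assessment at intervention completion as secondary. T2 and the eligibility ages need not change. The passages on intervention length should be reconciled separately; this point takes no view on when the intervention should end.

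Confirm that the chosen T3 can be reached by every enrollee within the 3-year funding, or state that collection continues beyond it.

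The cost is rewording and visit scheduling, and assessments at other times become secondary.

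### The overall remission objective is not matched by the outcome list or by the fixed secondary analysis: remission is not a listed outcome, and Wilcoxon tests on HBI or PUCAI each cover only one disease type

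*Protocol article*

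**What the plan says.** **Objective.** Under Outcome measures, Aim 1, the secondary clinical outcomes include calprotectin and either the HBI or the PUCAI, from which "we will assess whether the intervention improves overall remission rates". That paragraph refers the reader to Table 1 for the list of secondary outcomes. Table 1 holds the individualized-assessment questionnaires and contains no disease activity measure.

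**Outcome list.** Table 5 gives four disease activity measures:
- "Physician global assessment (PGA) of disease activity"
- "Modified Harvey Bradshaw Index (HBI) Assessment for CD Activity"
- "Pediatric Ulcerative Colitis Activity Index (PUCAI) for UC Activity"
- fecal calprotectin, collected "at enrollment and study termination only"

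The first three are scheduled at enrollment (T1), transfer (T2) and study end (T3). Remission does not appear as an outcome.

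**Analysis.** The Statistical analysis section says: "Secondary outcome measures will be analyzed at study completion and interim time points by comparing participants in the intervention and control arms", by the Wilcoxon-Mann-Whitney test. A repeated measures analysis over baseline, transfer and end of study is added for the primary and secondary measures alike. Logistic regression is named only for emergency department use and hospitalization.

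**The concern.** The objective is a rate, and it is meant to be overall. The outcome list consists of activity measures, and the stated between-arm method compares ranks. HBI and PUCAI are different scales for different diseases, so their raw scores cannot be ranked together. Applied to the listed measures, the stated method yields one HBI comparison among Crohn's participants and one PUCAI comparison among colitis participants. Neither is a remission rate and neither covers the whole sample.

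At stake is a useful secondary question: whether any gain in function comes with controlled disease. The text as it stands leads to two small subset tests. It makes no use of the T1 activity values in the between-arm comparison, although they are collected. Disease type is not a randomization stratum (the strata are center and IBD-DI severity), so the design does not protect balance within each subset. Calprotectin, one of the measures on which the remission statement rests, has no T2 value for the three-timepoint analysis.

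**Working it through.** **1. Reading the sections together**

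| Place | What it fixes |
|---|---|
| Aim 1, secondary clinical outcomes | A remission rate, across all participants |
| Table 5 | PGA, HBI (Crohn's), PUCAI (colitis), calprotectin (T1 and T3); no remission variable |
| Statistical analysis | Wilcoxon test between arms; three-timepoint repeated measures; logistic regression for ED use and hospitalization only |

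No step takes the reader from the second and third rows to the first.

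**2. Inputs for size**

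From the article: 90 enrolled, 25% drop-out, alpha 0.05. Completers are 90 × 0.75 = 67.5, or about 34 per arm. The article gives no Crohn's/colitis split and no remission rate, so both are assumed below. Tests are taken as two-sided.

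**3. Power formula and check on the article's own figure**

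For the Wilcoxon test with n per arm, set m = n × 3/π, df = 2m − 2 and noncentrality d√(m/2), and use the noncentral t distribution. At d = 0.78 with one-sided alpha 0.05 this gives 23 per group for 80% power and 31 for 90%. Those are the article's 46 and 62 in total. They concern the IBD-DI only. The match validates the formula and says nothing about remission.

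**4. Separate tests against one test on everyone**

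With 60% Crohn's (assumed), 34 × 0.6 = 20.4 and 34 × 0.4 = 13.6, so about 20 and 14 per arm. At d = 0.7 (assumed):
- n = 34: m = 32.5, noncentrality 0.7 × √16.2 = 2.82, power 79%
- n = 20: m = 19.1, noncentrality 0.7 × √9.55 = 2.16, power 56%
- n = 14: m = 13.4, noncentrality 0.7 × √6.68 = 1.81, power 41%

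The effects detectable with 80% power are d = 0.71, 0.93 and 1.13 respectively. A simulated van Elteren test (Wilcoxon stratified by disease, 20 + 14 per arm, d = 0.7 in both strata) also gives about 79%, so stratifying recovers what splitting loses.

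Sensitivity to the assumed share, two-sided power at d = 0.78:

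| Crohn's share | HBI per arm | Power | PUCAI per arm | Power |
|---|---|---|---|---|
| 50% | 17 | 58% | 17 | 58% |
| 60% | 20.4 | 66% | 13.6 | 48% |
| 70% | 23.8 | 73% | 10.2 | 37% |

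A measure available in all 34 per arm has 87%.

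**5. Power of a pooled yes/no comparison**

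z = [Δ√n − 1.96√(2p̄(1−p̄))] / √(p₁(1−p₁) + p₂(1−p₂)), with n = 34:
- 50% vs 70%: (1.166 − 1.358)/0.678 = −0.28, power 39%; 93 per arm needed for 80%
- 60% vs 80%: (1.166 − 1.270)/0.632 = −0.16, power 43.5%; 82 per arm needed
- 50% vs 80%: power 75%; 39 per arm needed

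Putting d = 0.7 on a normal latent scale and dichotomizing gives 50% vs 76% (power about 60%) or 70% vs 89% (about 49%).

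**6. Does the stated test rule out a rate?**

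For 24/34 against 17/34 in remission, the asymptotic Wilcoxon test gives p = 0.085 and the uncorrected chi-square p = 0.083. The stated test could be applied to a yes/no variable with almost the same result.

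**The case against.** The strongest reply is that nothing prevents the remission analysis. The choice of HBI or PUCAI reads naturally as each participant being classed on the index for their own disease, and the yes/no results could be pooled. Wilcoxon on a binary variable is nearly chi-square. PGA and calprotectin are tied to neither disease. Cut-offs and pooling rules commonly sit in an SAP or full protocol, which are not shown.

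Most of this stands, and it limits the point. A reader might infer any of the following, and the documents do not support them:
- **That remission cannot be derived.** The indices are scheduled at all three timepoints and the data are there.
- **That every activity test uses only part of the sample.** This is true of HBI and PUCAI, but not of PGA or calprotectin.
- **That the missing cut-offs are an error.** They may be written elsewhere.
- **That a cut-off would be chosen after seeing unblinded data.** Nothing in the text says so.
- **That calprotectin timing is a serious contradiction.** Table 5's specific entry reasonably overrides the general three-timepoint sentence, so an explicit exemption is enough.

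What the reply does not remove is the mismatch in what the article does state. The remission sentence does not name PGA as its basis. Table 5 does not list remission. The stated rule for secondary outcomes, applied to the listed measures, produces no overall remission result. The article names a binary method where it intends one, and does not do so here.

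**Conclusion.** The point holds as a mismatch on a secondary outcome. The article promises an assessment of overall remission rates that its outcome list and fixed secondary analysis do not deliver, and an unadjusted Wilcoxon test on either index alone covers one disease type. It should be corrected, but it does not touch the primary analysis.

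The size rests on assumptions. With a 60% Crohn's share and d = 0.7, separate tests have about 56% and 41% power against about 79% for one stratified test. A different split moves the two subset figures but leaves both below the whole-sample figure. Pooling remission as yes/no gives one coherent answer to the stated objective, but it is no power remedy: 39% to 44% for 20-point differences with 34 per arm, under assumed rates. The gain in power comes from the stratified score test.

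**What to change.** 1. List remission (yes/no) as a secondary outcome in Table 5. Class each participant on the index for their own disease, with a definition fixed before data review that also states the role of calprotectin and covers anyone labelled neither Crohn's nor colitis. Compare arms in one pooled analysis, for example logistic regression, adjusted for T1 remission and disease type.
2. Compare activity scores with one disease-stratified (van Elteren) test in place of separate HBI and PUCAI tests.
3. Compare log calprotectin at T3 adjusted for T1, and exempt calprotectin from the three-timepoint analysis because it has no T2 value.
4. Correct the reference to Table 1 for secondary outcomes so that it points to Table 5.

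**Cost:** wording in the protocol and SAP, with no new data or visits. Dichotomizing loses information and the pooled remission test has limited power, so report it with its confidence interval alongside the stratified score test.
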